##### Power and sample size

We computed power and sample size calculations using Pass 14 (Kaysville, UT). Based on the ERIC survey data from the HCV initiative [30], we anticipate receiving responses from at least 80 facilities and assume that the mean number of strategies implemented in the no facilitation arm will be 25 strategies with a standard deviation of 14. For aim 1a, we will have 80% power to detect a difference of 9.15 ERIC implementation strategies between the study arms using an alpha level of 0.05. Calculations are similar when allowing for different sample sizes with the ability to detect differences of 8.6 (90 facilities) to 9.75 (70 facilities) for varying facility responses. For aim 1b, the detectable difference in case review completion rates depends upon the sample size and the baseline completion rate in the no facilitation arm. Table 3 provides the difference in case review completion rates detectable in the facilitation arm for a variety of baseline completion rates and sample sizes. For example, assuming a 70% baseline completion rate and a sample size of 90, we have 80% power to detect an 11.6 percentage point difference in the case review completion rate in the facilitation arm, which is equivalent to an odds ratio of 1.91.

**Table 3 Tab3:** Power calculations for aim 1b

Baseline rate (%)	Sample size					
	70		80		90	
	∆* (%)	OR	∆* (%)	OR	∆* (%)	OR
50	+ 16.1	1.95	+ 15.2	1.87	+ 14.4	1.81
60	+ 14.8	1.98	+ 14.0	1.90	+ 13.3	1.83
70	+ 12.9	2.08	+ 12.2	1.98	+ 11.6	1.91
80	+ 10.2	2.31	+ 9.7	2.19	+ 9.3	2.09
90	+ 6.5	3.05	+ 6.2	2.84	+ 6.0	2.68

*Detectable difference from baseline case completion rate in the consequences (vs. no consequences) arm at a given sample size and with 80% power

#### Aim 2

We will use CFIR-based interviews to identify barriers and facilitators to implementing the policy notice and compare these barriers and facilitators across facilities with high and low adherence to recommended opioid therapy guidelines in each of the four randomization arms. Codebook construction will follow methods outlined by Crabtree and Miller for research conducted in a medical context [36]. We will employ a system of audit trails to document the creation of codes. For each code, the codebook will specify inclusion/exclusion criteria and textual examples of clear and borderline cases. Representative quotations will be captured verbatim from the transcripts using Atlas.ti. As part of the coding process, the analysts will meet and process any differences in the assessment of codes for each case until agreement is achieved. The codes determined through this agreement process will then be recorded in a master file, which will become the basis for the final analysis. This process of coding independently (the basis for the inter-coder reliability scores) and then discussing each case will aid in achieving high levels of inter-coder reliability.

In addition to qualitative data analysis, the coded text data from the CFIR interviews will be used to make the numerical ratings for the individual subdomains under the four domains included. In general, ratings are determined based on two aspects: (1) valence (positive or negative impact on implementation) and (2) strength (the degree to which implementation was facilitated or hindered, with possible choices being 0, 1, or 2) [20]. The valence component of a rating is determined by the influence the coded data exhibits on the implementation process; that is, is the subdomain in question broadly facilitating or hindering? The strength of a rating has several determinants, including level of agreement among participants, strength of language, use of concrete examples, and stated influence on implementation or another subdomain. Considering both the valence and the strength of each subdomain, the rating scale ranges from + 2 (most facilitating) to − 2 (most hindering). A zero rating reflects a neutral (e.g., statements lacking sufficient information to make a clear scoring distinction) or mixed influence of the code (e.g., statements indicating equal presence and absence of a subdomain and having no impact on implementation). A team will meet and review all the comments associated with a specific construct, and then assign a rating. Each construct will be rated for each arm of the study, allowing for detailed descriptions of barriers and facilitators across arms. This CFIR rating process also creates an overall picture of how the domains differ across arms, providing guidance for future implementation efforts.

#### Merging data from aims 1 and 2

In addition to separately analyzing the ERIC survey data and the CFIR-based interviews, we will merge these two data sources as described by Creswell & Plano Clark [29]. This integration will be done to assess the degree to which the most common implementation strategies that significantly predict case review completion rates are matched with certain barriers identified by the CFIR interviews. Then, these results could be compared to the work of Damschroder, Powell, and colleagues [37] who used an expert panel to begin to determine which strategies are best suited to address barriers across various CFIR domains.

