To augment these monthly metrics, the Office of Mental Health and Suicide Prevention (OMHSP) and the National Pain Management Program developed a predictive model to estimate the risk of serious adverse events (or SAEs, i.e., suicide-related events, overdoses, overdose deaths) among patients who are prescribed opioids. OMHSP translated the predictive model into the Stratification Tool for Opioid Risk Management (STORM). OMHSP developed STORM to empower facilities and clinicians to provide targeted opioid risk mitigation strategies to the most at-risk Veterans [17]. Using data from electronic medical records on demographics, previous overdose or suicide-related events, prescriptions, substance use and mental health disorders, and medical co-morbidities, the STORM algorithm calculates a “risk score” of SAEs for each Veteran who is prescribed opioids [17]. Updated nightly and based on the underlying predictive model, the STORM dashboard displays the estimated % chance of experiencing an SAE for each Veteran as well as their level risk categorized as low, medium, high or very high (for filtering purposes). The STORM dashboard also displays various risk factors that apply to each patient, including relevant diagnoses, prescriptions (opioid, pain, sedation), and use of risk mitigation strategies (including non-pharmacologic treatments). Finally, to support care coordination, the STORM dashboard also displays upcoming appointments to primary care, mental health, pain clinic, or other treatment sources.

In March of 2018, the VA released a national policy notice requiring all VA Medical Centers (VAMCs) to conduct data-based case reviews of patients with opioid prescriptions that STORM identifies as having very high risk of SAEs. Case reviews entail using the STORM dashboard and/or other data-based procedures (e.g., consulting state Prescription Drug Monitoring Programs) to evaluate each patient’s risk level and determine whether additional risk mitigation strategies (e.g., referral to pain specialist, prescription of naloxone kit) are indicated for that patient. The completed case review and any actions taken by the clinician are documented using a standardized note in the VA electronic medical record and in the STORM dashboard.

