Additional analyses will assess the association between the type of implementation strategies used and the case completion rate. We will assess the association between each individual strategy and case review completion in individual regression analyses. We will also assess the relationship between the percent of implementation strategies used within each cluster of strategy types and case review completion rates. Because we have adapted the ERIC survey for this evaluation, we will conduct confirmatory factor analyses to verify that the original clusters were maintained. If the factor analysis does not confirm the original clusters, we will describe the resulting strategy type factors and utilize summary scores based on the new factors. Finally, we will assess whether the overall number of implementation strategies used mediates the relationship between randomization arm and case review completion rate. We will test mediation using the bootstrapping methods of Preacher and Hayes [35]. These methods will allow for the direct estimation and testing of mediation and do not make any distributional assumptions (such as normality) regarding the variables or the test statistic. Analyses are based on taking a large number of bootstrap samples with replacement from the original data and estimating effects for each sample. The mean estimated effect and empiric confidence intervals are computed across all samples. Furthermore, because inferences do not depend upon large-sample theory, this method can be used for data with smaller sample sizes.

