OMHSP is interested in understanding whether and how the case reviews of patients at very high risk of opioid-related SAEs get incorporated into practice and the factors that affect the ability of VAMCs to carry out such case reviews effectively. Understanding whether including facilitation (vs. no facilitation) in the policy notice increases facility compliance will inform future policy development. Testing the effect of adding new patients into the STORM risk group for whom case reviews are required will yield insights regarding which patients should be targeted for case reviews to achieve the desired reduction in opioid-related SAEs. The implementation evaluation will complement the analysis of changes in opioid-related SAEs over time and across randomization arms. We will be able to learn which implementation strategies are most effective in supporting case reviews, and how that relationship differs between the facilitation (which itself is an implementation strategy) and no facilitation arms. We will also be able to learn which barriers and facilitators, using CFIR, are most salient across the four arms. Finally, combining data on implementation strategies and barriers at such a large scale could advance implementation science by showing which strategies are naturally best suited to address certain barriers.

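### Table 3 is labelled as a facilitation-arm difference at 70 to 90 survey responders, but its figures are a per-SD regression effect; as an arm contrast on a facility-level yes/no outcome they carry 19-28% power, not 80%

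*Protocol article*

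**What the plan says.** In the protocol article, the Power and sample size section starts from the survey: "we anticipate receiving responses from at least 80 facilities", with 70 and 90 as alternatives. For aim 1b it then says that Table 3 shows "the difference in case review completion rates detectable in the facilitation arm for a variety of baseline completion rates and sample sizes". The worked example reads: "assuming a 70% baseline completion rate and a sample size of 90, we have 80% power to detect an 11.6 percentage point difference", given as an odds ratio of 1.91. The Table 3 footnote repeats that the difference is between the arms with and without consequences, "at a given sample size and with 80% power".

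The Aim 1b section describes a different primary analysis. Completion at 6 months is regressed on the number of strategies reported in the survey. Arm enters aim 1b only through the mediation analysis: "we will assess whether the overall number of implementation strategies used mediates the relationship between randomization arm and case review completion rate".

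Completion does not depend on the survey. The Background says: "The completed case review and any actions taken by the clinician are documented using a standardized note in the VA electronic medical record". Trial status says that 141 facilities were randomised and that the programme office contacted those below the 97% target. The Background also assigns the effects of facilitation, with completion as an intermediate outcome, to the partner evaluation, which uses administrative and clinical data.

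**The concern.** Two things look wrong.

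First, the power statement names a randomised contrast but gives it the sample size of a survey. If the contrast is meant, the survey N is the wrong N. If the strategy-count association is meant, the label is wrong. In either case a reader takes away an 80% power claim for the arm comparison. The Discussion gives that comparison weight: "Understanding whether including facilitation (vs. no facilitation) in the policy notice increases facility compliance will inform future policy development".

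Second, the mediator exists only for responders, so the arm-to-completion effect that the mediation analysis splits into direct and indirect parts would be a responder effect. The survey opened about six months after the arm-specific notices went out. Whether a site's point of contact responds may depend on arm and on how the site is performing. The responder effect could therefore differ from the all-site effect examined by the partner evaluation, and the plan does not say how the two would be reconciled.

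**Working it through.** **Inputs.** Alpha 0.05 is stated with aim 1a ("using an alpha level of 0.05") and not separately for aim 1b. Sidedness is not stated; two-sided is assumed because it reproduces the table. Power is 80%, responders number 70, 80 or 90, and 141 sites were randomised 1:1 to facilitation.

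**Step 1: reproduce Table 3.** Use the sample-size formula for logistic regression on one standardised continuous covariate, where P is the event rate at the covariate mean and OR is per 1 SD:

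N = (1.960 + 0.842)² / [P(1−P)(ln OR)²] = 7.849 / [P(1−P)(ln OR)²]

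Worked example, P = 0.70 and OR = 1.91: 7.849 / (0.21 × 0.647²) = 89.3, against the stated 90. In reverse, N = 90 gives ln OR = 2.802/√(90 × 0.21) = 0.644 and OR = 1.90. The odds move from 0.70/0.30 to a rate of 81.6%, a difference of 11.6 points as stated.

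Over all 15 cells the formula returns N of 69.7-70.4, 79.4-80.1 and 89.2-90.3. Every difference agrees to 0.1 point and every OR within 0.01. A one-sided test gives about 55, 63 and 71 and does not fit.

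**Step 2: read the same cells as labelled.** Two-arm comparison of a facility-level yes/no outcome (target met or not), 45 per arm, 70% v 81.6%:

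- SE under no difference (pooled rate 0.758): √(2 × 0.758 × 0.242/45) = 0.0903
- SE under the alternative: √[(0.70 × 0.30 + 0.816 × 0.184)/45] = 0.0895
- Power = Φ[(0.116 − 1.960 × 0.0903)/0.0895] = Φ(−0.68) = 0.25

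Reaching 80% would take about 426 facilities. Over the whole table power is 19-28%, and 294 to 566 facilities would be needed. Treating N as the number per arm does not rescue the label (33-50% power).

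**Step 3: what an arm contrast can detect** (same test, 80% power, 70% baseline).

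| N | Detectable difference, two-arm | Table 3 formula, per SD |
|---|---|---|
| 90 | 22.7 points | 11.6 points |
| 141 | 18.9 points | 9.6 points |

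At N=141 the two-arm figure is 22.8 points at a 50% baseline and 15.4 at 80%.

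**Step 4: the responder effect inside the mediation.** SE relative to all 141 sites is √(141/N): 1.42, 1.33 and 1.25 at N = 70, 80 and 90, which is 50%, 57% and 64% of the randomised sites.

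The bias from selection cannot be computed from the document. As an illustration with assumed response rates and no true arm effect, let 60% of sites in each arm meet the target and let response in the no-facilitation arm (57%) be unrelated to meeting it. If 67% of meeting and 43% of non-meeting facilitation sites respond, responders show 0.402/(0.402 + 0.172) = 70% v 60%, OR 1.56. With 60% and 52% responding, the OR is 1.15. In the first case overall response is 57% in both arms, so equal response rates would not reveal the problem.

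**The case against.** The strongest reply is that no stand-alone arm comparison among responders is planned, and that is correct. The primary model of aim 1b uses the strategy count, so it needs the survey, and 70 to 90 responders is the right N for it. The mediation also needs the survey. The all-site effect of facilitation on completion belongs to the partner evaluation. A reader might infer from the Table 3 label that the randomised contrast will be run on responders and that randomisation is thereby broken for the main question. The document does not support that. What stands is narrower: the label, the power claim attached to it, and a total effect inside a secondary analysis.

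A second reply is that aim 1b may model the proportion of reviews completed instead of target met. Power for an arm contrast then depends on the between-site SD, which is not given. With assumed SDs of 10, 20 and 30 points, the detectable difference is 6.3, 12.7 and 19.0 points at 80 sites and 4.8, 9.5 and 14.3 at 141. An SD near 19 points (20 × 12.2/12.7) would bring the 80-site figure to the table's 12.2 at a 70% baseline. That agreement would be a coincidence, because the table was not built from such an SD. It does mean that the 19-28% applies to the yes/no outcome only.

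A third reply is that 80 is described as a minimum and all 141 contacts are invited. A higher response would shrink the precision loss, and the selection odds ratios rest on response rates that the document does not contain. Both points are fair.

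**Conclusion.** The point holds as a mislabelled power table plus a reporting gap in the mediation analysis.

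Table 3 describes the association with a continuous predictor per SD, and the text and footnote call it a facilitation-arm difference. For that contrast the claimed 80% is 19-28%, assuming a yes/no outcome per facility, 1:1 arms and a two-sided 0.05 test. A reader might infer that putting 141 in place of 70 to 90 repairs the table. It does not: the table's own formula then gives 9.6 points at a 70% baseline, whereas a two-arm contrast needs 18.9.

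The responder-only arm effect in the mediation has an SE 1.25 to 1.42 times that at 141 and is open to selection after randomisation. The direction and size of any bias are unknown. Since the partner evaluation examines the all-site effect, the consequence is two possibly different arm effects on one outcome; the randomised answer itself is not lost.

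**What to change.** - Relabel Table 3, its footnote and the worked example as the association of completion with strategy count, with the OR per 1 SD of that count, at 70 to 90 responders.
- If an arm difference is to be stated, recompute it as a two-arm contrast at N=141: about 19 points at a 70% baseline for meeting the target. For the proportion completed, state the between-site SD assumed.
- Report the effect of randomised arm on completion at 6 months in all 141 sites, from one extra model or from the partner evaluation, beside the responder total effect in the mediation, as a check on selection. Use responders only for the paths that need the strategy count.

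The cost is an edit to the table and at most one model on data already held. There are two drawbacks: direct plus indirect effects will not sum exactly to the all-site total, and the stated detectable arm difference for meeting the target will look less favourable than the present table suggests.

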#### Aim 1b

The primary analysis for aim 1b will estimate the association between number of implementation strategies used and completion of case reviews at *T*_0_ + 6 months. If enough VAMCs meet the 97% target completion rate, we will analyze the data using logistic regression for the outcome of meeting the target rate; otherwise, we will model the proportion of case reviews completed. The outcome will be modeled using a generalized linear model with logit link and binomial family. This strategy will appropriately model the case review completion rates as being restricted between 0% and 100% and is equivalent to logistic regression for binary (yes/no) outcomes. For these analyses, the number of implementation strategies used will be the independent variable and will be coded as either continuous or categorical. Because difficulty in completing case reviews could increase as volume of very high-risk patients increases, we will include the number of very high-risk patients at each facility as a predictor along with the other facility variables.

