There are important limitations that also must be considered. Most importantly, this intervention is occurring in the context of many other national, regional, and local opioid safety initiatives emerging or already in place. The randomized design is an important method to address this concern, and the ERIC survey and qualitative interviews will elucidate how other initiatives impact particular facilities during the course of the trial. Second, any survey targeting employees and providers will have challenges achieving an adequate response rate, especially given the length of the survey and inability to incentivize respondents. However, the previous use of the ERIC survey in a similar initiative achieved a good response rate (74%) and found that respondents who started the survey completed the survey, with no bias towards endorsement of strategies presented earlier in the survey [30]. Finally, the evaluation is at the facility level, meaning there will be ERIC data on no more than 141 sites. Power is thus limited to detect small differences across arms and to control for all the potentially relevant organizational covariates. However, we are maximizing the chance of finding an effect by using a rigorous randomized approach that includes all VAMCs.

In sum, the evaluation of implementation factors will provide valuable insights into how VAMCs implement a policy designed to reduce opioid-related SAEs among Veterans and will identify types of implementation strategies that are associated with successful implementation. The resulting data from the evaluation described here will help OMHSP and other VA decision makers prioritize which types of implementation strategies to recommend and use in future policy rollouts and implementation initiatives.

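### Table 3's 80% power for aim 1b is an unadjusted one-predictor figure, so it is an upper bound for the covariate-adjusted primary model, and its effect is per 1 SD of strategy count, not an arm difference

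*Protocol article*

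**What the plan says.** Power and sample size (Protocol article) gives the only power statement for aim 1b. It expects data from a limited set of sites ("we anticipate receiving responses from at least 80 facilities"), and the worked example reads "assuming a 70% baseline completion rate and a sample size of 90, we have 80% power to detect an 11.6 percentage point difference", "which is equivalent to an odds ratio of 1.91". The text presents the effect as an arm contrast: "Table 3 provides the difference in case review completion rates detectable in the facilitation arm". The table footnote does the same: "Detectable difference from baseline case completion rate in the consequences (vs. no consequences) arm at a given sample size and with 80% power". Neither the text nor the table mentions covariates.

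Aim 1b defines the primary analysis as the association between the number of strategies used and case review completion. The outcome is yes/no (97% target met) if enough sites meet the target, and otherwise the proportion of reviews completed. The strategy count is the independent variable, and "we will include the number of very high-risk patients at each facility as a predictor along with the other facility variables". Table 1 lists 13 facility characteristics planned for inclusion. The section that introduces them makes their use depend on data availability and describes it as partly descriptive and exploratory.

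The Discussion concedes a limit without a figure: "Power is thus limited to detect small differences across arms and to control for all the potentially relevant organizational covariates".

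**The concern.** Power for a regression coefficient falls as the predictor of interest becomes better explained by the other terms in the model. If Table 3 was computed for a model with the strategy count alone, its 80% does not describe the planned primary model, which also holds review volume and facility variables. These variables may well be related to the strategy count, since the article itself expects size, resources and organisation to shape implementation.

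The practical risk lies in interpretation. A null adjusted association between strategies and completion would be read against 80% power at the printed effects, although the fitted model would have less.

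**Working it through.** **Inputs.** Power 80%, N = 70, 80 or 90 facilities and baseline rates P of 50% to 90% come from Table 3. Alpha is given for aim 1a ("using an alpha level of 0.05"). I assume that it carries over to aim 1b; taking it as two-sided reproduces the table. No R-squared between the strategy count and the covariates appears anywhere, so every value used below is an assumption.

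**Step 1: reproduce Table 3.** For one standardised continuous predictor with R-squared = 0:

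ln(OR) = (1.960 + 0.842) / √(N·P·(1 − P))

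At P = 0.70 and N = 90: √(90 × 0.21) = 4.347; 2.802/4.347 = 0.644; OR = 1.905. The rate moves from 70% to 81.6%, or +11.6 points (printed: +11.6, OR 1.91). All 15 differences agree to 0.1 point and all 15 odds ratios to within 0.01.

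An arm comparison does not reproduce the table. For 70% against 81.6% with 45 facilities per arm, two-sided power is about 25%, and 80% power would need 213 per arm. Across the 15 cells the two-sided figure is 19–28%. The printed effect is therefore the change per 1 SD of the strategy count. The formula also treats each facility as one yes/no outcome, so it matches only the 97%-target branch.

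**Step 2: count the covariate terms.** Coded as in Table 1: visit quartiles 3, complexity 4, region 3, and ten characteristics at one term each (academic detailing counted as one). That makes 20, and review volume makes 21. Smaller sets are also compatible with the text: volume alone (1), the four facility-structure variables (3 + 1 + 4 + 3 = 11), or 14 terms (for example, 13 characteristics at one term each plus volume).

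**Step 3: adjust.** The same formula replaces N by N(1 − R²), so power at the printed effect is

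Φ(2.802·√(1 − R²) − 1.960)

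If the k covariate terms are unrelated to the strategy count, the expected in-sample R² is k/(N − 1):

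| Covariate terms | N = 70 | N = 80 | N = 90 |
|---|---|---|---|
| 1 (volume only) | 79.4% | 79.5% | 79.6% |
| 11 | 72.9% | 73.9% | 74.6% |
| 14 | 70.6% | 71.9% | 73.0% |
| 21 | 64.7% | 67.0% | 68.8% |

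For example, 21 terms at N = 90 give R² = 21/89 = 0.236, and Φ(2.802 × 0.874 − 1.960) = Φ(0.489) = 68.8%.

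**Step 4: worked example (70%, N = 90) over assumed R².** The detectable ln(OR) is 0.644/√(1 − R²).

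| R² | Power at printed effect | Detectable OR | Detectable change |
|---|---|---|---|
| 0 | 80% | 1.91 (printed) | +11.6 |
| 0.10 | 76% | 1.97 | +12.2 |
| 0.25 | 68% | 2.10 | +13.1 |
| 0.40 | 58% | 2.30 | +14.3 |

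**The case against.** The arithmetic of Table 3 is correct for the model it uses, and the dispute is over an unstated assumption. Five points can be made against the concern.

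- **The covariate set is not fixed.** The facility variables depend on data availability and are partly exploratory, and Aim 1b gives no count. This stands. A reader might infer a fixed loss of 11 to 15 points, but that requires all 21 terms (or an assumed R² of about 0.24 to 0.30). With volume alone the chance loss is about half a point, and with 11 to 14 terms it is 5 to 9 points.
- **k/(N − 1) is an in-sample expectation placed in a planning formula, and a planner may assume a smaller correlation.** This stands in part. It is why the result is given as a range. It does not make zero the right value for a model that enters several facility variables.
- **Arm is randomised, so R² = 0 is natural for an arm contrast.** That is true of an arm contrast, but the primary aim 1b predictor is the strategy count, and Table 3 does not reproduce as an arm contrast. This objection exposes the mislabelled effect and does not rescue the 80%.
- **The Discussion already discloses limited power for covariate control.** It does so without a figure, and Table 3 still prints 80% unqualified.
- **More sites may respond.** All 141 are invited. Under the k/(N − 1) rule with 21 terms, 101 responders would carry about the information of the N = 80 column (101 × 0.79 = 79.8). This is fair, but the table is indexed by N, and each column still overstates power for that N.

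A reader might go further and infer that the planned model keeps only two-thirds of the stated sensitivity, or that the 90% row cannot be fitted at all. The figures do not support the first: 65–69% against 80% is 81–86% of the stated power. The second would concern only the yes/no branch with every covariate entered, whereas Aim 1b switches to the proportion of reviews completed if too few sites meet the target.

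**Conclusion.** The concern holds as a mismatch between two parts of the article. The printed 80% belongs to an unadjusted one-predictor model, and the primary analysis is specified with covariates. Within the plan's own formula, 80% is an upper bound.

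The size depends on what is entered and how strongly it correlates with the strategy count. The loss is about half a point with volume alone, 5 to 9 points with 11 to 14 terms, 11 to 15 points with the full Table 1 set under chance correlation, and about 22 points at an assumed R² of 0.40. No single figure can be derived from the documents.

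These results assume two-sided alpha 0.05 and the yes/no 97%-target outcome. They do not transfer to the proportion-completed branch, for which the article gives no matching calculation. The effect must also be read as per 1 SD of strategy count, so correcting the number while keeping the facilitation-arm label would leave the sentence wrong.

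**What to change.** 1. Label Table 3 and the worked example as unadjusted, and as the change in the probability of meeting the 97% target per 1 SD of strategy count. Remove the description as a difference in the facilitation arm from the text and the footnote.
2. State how many covariate terms the primary aim 1b model is assumed to contain.
3. Rerun the table with N multiplied by (1 − R²) over a stated range such as 0.10 to 0.40. For 70% and N = 90, report about +12.2, +13.1 and +14.3 points at 0.10, 0.25 and 0.40, or equivalently 76%, 68% and 58% power at the printed effect. Limiting the covariate set and reporting power for that set would also serve.
4. Say that the table does not cover the proportion-completed branch.

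The cost is one rerun of the same routine, a revised table and a few sentences. It needs no extra sites or data. The only downside is less favourable stated figures.

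### Table 3 and the aim 1b power example match a per-SD regression calculation but are labelled as a difference between facilitation arms

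*Protocol article*

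**What the plan says.** Under Power and sample size, the worked example for aim 1b takes a baseline of 70% and 90 facilities, and states: "we have 80% power to detect an 11.6 percentage point difference in the case review completion rate in the facilitation arm". It puts the matching odds ratio at 1.91. The detectable difference is said to depend on two things: it "depends upon the sample size and the baseline completion rate in the no facilitation arm". Table 3 gives a difference and an odds ratio for five baseline rates (50% to 90%) and three sample sizes (70, 80, 90). Its footnote labels the differences: "Detectable difference from baseline case completion rate in the consequences (vs. no consequences) arm". The same footnote sets the power at 80%. The sample sizes are counts of responding facilities.

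The section Aim 1b describes a different analysis: "The primary analysis for aim 1b will estimate the association between number of implementation strategies used and completion of case reviews". There the independent variable is the strategy count, not the arm. The outcome is either the yes/no 97% target, if enough centres meet it, or else the proportion of reviews completed. Arm enters aim 1b only through the mediation analysis.

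**The concern.** The only power statement for aim 1b names a contrast (arm) that is not the primary analysis of that aim, and the numbers do not behave like a two-arm comparison. With 45 facilities per arm and one yes/no result each, 70% against 81.6% is far too small a gap to be found 80% of the time.

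Two things are at stake. A reader could take a null arm result as evidence against differences of 6 to 16 points that the comparison may not have been able to detect. And the analysis that the numbers do describe, completion against number of strategies, is left without a correctly labelled power statement.

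**Working it through.** **Inputs.** Baseline rates, sample sizes, differences and odds ratios come from Table 3, and power is 80%. Alpha is stated for aim 1a only ("using an alpha level of 0.05"); I carry it over to aim 1b and take it as two-sided. Half of the centres received the facilitation notice, so I take 35, 40 or 45 facilities per arm. The SD of the strategy count is 14, from the aim 1a assumptions.

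**Step 1: reproduce the plan's figures.** For one normally distributed covariate in logistic regression, with p the event rate at the covariate mean and the odds ratio per 1 SD:

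ln(OR) = (1.960 + 0.842) / √(N·p·(1−p))

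- 70%, N = 90: 2.802/√18.9 = 0.644, so OR 1.90 to 1.91. Odds 2.333 × 1.905 = 4.445, so the rate is 81.6% and the difference +11.6. Stated: +11.6, OR 1.91.
- 50%, N = 70: 2.802/√17.5 = 0.670, OR 1.95, difference +16.1. Stated: +16.1, OR 1.95.
- 90%, N = 80: 2.802/√7.2 = 1.044, OR 2.84, difference +6.2. Stated: +6.2, OR 2.84.

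All 15 cells agree: every difference to 0.1 point and every odds ratio to within 0.01. Power at the stated odds ratios is 79.8% to 80.4%.

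**Step 2: try the contrast that the text names.** Two proportions, N/2 facilities per arm, pooled z test, two-sided 0.05. For 70% vs 81.6% with 45 per arm:

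- Null SE = √(2 × 0.758 × 0.242/45) = 0.0903
- Alternative SE = √((0.700 × 0.300 + 0.816 × 0.184)/45) = 0.0895
- Power = Φ((0.116 − 1.960 × 0.0903)/0.0895) = Φ(−0.68) ≈ 24.8%

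| Baseline | Power at the Table 3 difference, N = 70 / 80 / 90 | Difference with 80% power, N = 70 / 80 / 90 |
|---|---|---|
| 50% | 27.3 / 27.7 / 27.9% | 31.3 / 29.5 / 28.0 points |
| 60% | 25.9 / 26.3 / 26.5% | 28.7 / 27.2 / 25.9 points |
| 70% | 24.3 / 24.6 / 24.8% | 25.0 / 23.8 / 22.7 points |
| 80% | 22.1 / 22.5 / 22.9% | 19.8 / 18.9 / 18.2 points |
| 90% | 18.8 / 19.1 / 19.8% | none reaches 80% |

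The reason is simple: a 1:1 arm indicator has SD 0.5, so an odds ratio per 1 SD is not an odds ratio between arms.

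**Step 3: other readings of the arm contrast.** Power at the stated differences is 28.6% to 39.5% one-sided, 17.8% to 27.9% with a Wald test on the log odds ratio, and 33.3% to 49.7% if N is per arm. A one-sample test against a fixed baseline gives 40.5% to 79.0%: near 80% in the 50% row only. None reproduces the table.

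**Step 4: if the proportion completed is the outcome.** The power to find 11.6 points with 45 per arm then depends on the between-facility SD. For 80% power, SD = 11.6/(2.802 × √(2/45)) = 11.6/0.591 = 19.6 points. With assumed SDs of 15, 20, 30 and 40 points, power is about 96%, 79%, 45% and 28%.

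**Step 5: is the problem wider?** No. The aim 1a figures (9.75, 9.15 and 8.6 strategies at 70, 80 and 90 facilities, SD 14) reproduce as a two-arm rank test with about 80% power.

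**The case against.** Four objections deserve an answer.

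- **The low power is conditional.** The text speaks of a completion rate, and the Aim 1b section makes the yes/no target only one of two possible outcomes. If facility proportions are compared and vary by less than about 20 points, 11.6 points is detectable with 90 facilities. This stands, and it limits the size of the finding. It does not rescue the table, whose figures use the facility count with variance p(1−p) and no between-facility SD.
- **The arm contrast is not the primary analysis here.** The Background assigns the effects of facilitation, including on review completion, to the separate clinical evaluation, and the Discussion concedes limited power for small differences between arms. This makes over-reading less likely. A general caveat still does not correct a specific 80% claim, and the Discussion also presents the effect of facilitation on compliance as something that will inform policy.
- **The numbers are usable for the primary predictor.** That is right. A reader might infer that the primary analysis of aim 1b was never powered; the documents do not support that. The calculation suits it for a yes/no outcome, and the label is what is wrong.
- **The origin is inferred.** The article names the software but not the procedure. The agreement in all 15 cells, on both the difference and the odds ratio, leaves little doubt.

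A reader might also infer that 70 to 90 responders is the wrong sample size. It is not: both the predictor and the mediator of aim 1b come from the survey, so responders are the analysable facilities.

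**Conclusion.** Table 3, its footnote and the worked example are mislabelled. They reproduce as the odds ratio detectable per 1 SD of a continuous covariate, about 14 strategies, with each facility contributing one yes/no outcome. They are not arm differences detectable with 80% power.

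For a yes/no facility target, equal arms and a two-sided 5% test, arm-contrast power at the tabulated differences is about 19% to 28%, and about 25% for the example. From a 70% baseline the differences detectable with 80% power are 25.0, 23.8 and 22.7 points, against the stated 12.9, 12.2 and 11.6. It would be too strong to say that the arm contrast has 19% to 28% power whatever the outcome. For the proportion completed the power cannot be fixed from the document, because the between-facility SD is not given. The error is confined to aim 1b and does not affect the design, the sample or any planned analysis.

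**What to change.** 1. Relabel Table 3, its footnote and the worked example as the detectable odds ratio per 1 SD of the number of strategies (about 14), for the yes/no target with the facility as the unit. Define the baseline as the rate at the mean number of strategies, and say that the figures are before adjustment for patient volume and the other facility variables.
2. Delete the statement about the facilitation arm, or replace it with a two-group calculation that names its outcome type. For the yes/no target at 90 facilities, this would be about 70% vs 92.7% (70 + 22.7). For the proportion completed, it should state the assumed between-facility SD and show a range.
3. State that alpha for aim 1b is 0.05 and whether it is two-sided.

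The cost is a correction of text and table, with no new data. The downside is that the arm-contrast figures become less favourable. An arm comparison of completion across all 141 centres is optional: it would be an added analysis overlapping the clinical evaluation, and is not part of this correction.
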